### Side-effects reporting

All adverse events will be described in patient file during consult at any of the follow-up visits or any other moment if indicated or requested by the patient. Serious adverse events will be reported through the web portal *ToetsingOnline* to the Medical Ethical Review Committee of the Academic Medical Centre of the University of Amsterdam, which approved the protocol, within 15 days after the sponsor has first knowledge of the serious adverse reactions.

### Data collection and follow up

Baseline characteristics will be obtained after randomisation but before treatment takes place. During follow up patients will be asked to return to the hospital for follow up at; one, three and six weeks and three, six and twelve months, according to standard Dutch protocols [8]. During these visits patients will be asked about any complaints and/or complications and physical and radiological examination will be performed. For details, see Table 1. Procedures additional to standard care are highlighted.

**Table 1 T1:** Follow-up visits

**Follow-up at:**	**Tests:**
1 week	VAS, X-ray
3 weeks	VAS, X ray
6 weeks	VAS, ROM, Grip strength, QoL, X-ray, PRWE, DASH
3 months	VAS, ROM, Grip strength, QoL, X-ray, PRWE, DASH
6 months	VAS, ROM, Grip strength, QoL, X-ray, PRWE, DASH
12 months	VAS, ROM, Grip strength, QoL, X-ray, PRWE, DASH

Examinations additional to stand care are bold.

### Sample size

This sample size calculation is based on the primary endpoint, the DASH score. The DASH score of an individual without any complaints of the wrist is 0. The mean DASH score after closed reduction and cast treatment after one year of follow up is 19 with a standard deviation (SD) of 18 [25]. This figure was measured in a patient population in which 72% suffered from a displaced extra-articular distal radius fracture. We assume that treatment with volar plating will decrease the DASH score which is achieved by conservative cast treatment by 15 points, from 19 to 4. Therefore at α = 0.05% and a power of 90%, with an estimated lost to follow-up of 10%, we would require 66 patients in total and 33 per treatment arm, to participate in the trial. This figure was calculated using the standard formula for means of superiority trials: n = [A + B]^2^ * 2 * SD^2^/DIFF^2^, where N = the number of patients required per arm, A the level of significance, B the power, SD the standard deviation of the primary outcome and DIFF the difference between the means. For safety measures and to correct for natural deaths, 45 patients in each arm will be included. From a separate study being conducted at the Academic Medical Centre Amsterdam and two other teaching hospitals, it was established that of the 703 distal radius fractures encountered in one year, 328 were an AO type A2 and A3. Therefore we estimate that we require a maximum of two years to include and follow up the patients in this trial.

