### Exclusion criteria

• Open distal radius fractures

• Multiple trauma patients (Injury Severity Score (ISS) ≥16)

• Other fractures of the affected extremity

• Patients who indicate to have had impaired wrist function prior to injury, for example due to rheumatoid arthritis, neurological disorders of the upper limb or previous malunions in the affected limb.

• Patients suffering from disorders of bone metabolism known to adversely effect fracture healing, such as osteomalacia.

• Patients suffering from connective tissue or (joint) hyperflexibility disorders known to adversely effect fracture healing and/or soft tissue and wound healing.

• Patients unable to understand the treatment information and informed consent forms as judged by the attending physician.

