### Primary outcome

The primary endpoint of this study is wrist function, pain and disability as measured with the DASH score at one year follow up [20]. The Disabilities of the Arm, Shoulder and Hand (DASH) score is a 30-item, self-report questionnaire designed to measure physical function and symptoms in patients with any or several musculoskeletal disorders of the upper limb. The DASH outcome measure is scored in two components: the Disability/Symptom and the optional high performance Sport/Music module. The DASH Disability/Symptom score is a summation of the responses to 11 questions on a scale of 1 to 5, with 0 (no disability) to 100 (severe disability). The questions test the degree of difficulty in performing a variety of physical activities because of arm, shoulder, or hand problems (6 items). It also investigates the severity of pain, tingling (2 items), as well as the effect of the upper limb problem on social activities, work, and sleep (3 items).

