### Benefits and risks assessment, group relatedness

The treatment that patients will receive is a component of the standard treatment of care, which currently depends on the surgeon’s preference and the complexity of the fracture. Patients will be asked to return to the hospital for follow up at one, three and six weeks, three months, six months and at twelve months. All visits are part of standard care following a fracture treated in this hospital. During these visits patients will be asked about any complaints and/or complications and physical examination will be performed. The assessment of the range of motion of the wrist will take approximately five minutes. Additional to standard care, patients will be asked to fill out three questionnaires at six weeks, three months, six months and one year. Patients will be asked to fill out a DASH form, rate their pain on a Visual Analogue Scale and give an estimation of the type and quantity of pain medication taken during all visits. This will take approximately ten minutes of their time. The PRWE score and the SF-36 will approximately take another ten minutes each. Subjects could experience mild discomfort during physical examination and testing, but this will be no different from that experienced during physical examination during routine follow-up. X-rays will be taken during every visit of which only the final radiographs at one year are additional to standard care. The burden experienced regarding time spent is difficult to estimate but will most likely not exceed 30 minutes. In the total duration of this study, patients will spend an approximate 150 minutes more. The risks are comparable to those that the standard treatment involves. This comprises the standard risk for undergoing a surgical procedure, including risks related to anaesthesia, neurovascular damage and post-operative wound infection. The risks of plaster immobilisation include redisplacement, malunion, loss of function, carpal tunnel syndrome and complex regional pain syndrome. Close follow up and a protocol of treatment, identical to the standard one, will be applied in every subject. Reduction of risks will be done according to inclusion and exclusion criteria. If complications arise, the treating physician will proportionate the adequate treatment according to the current protocols of treatment based on the published literature.

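### The primary DASH scores the whole upper limb, but no pre-injury DASH is listed or adjusted for; recalling one before allocation is a cheap gain in precision

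*Protocol article*

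**What the plan says.** All of the following is in the Protocol article.

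- **Scope of the endpoint.** Primary outcome presents the DASH as an instrument for musculoskeletal disorders anywhere in the upper limb. Its items ask about difficulty "in performing a variety of physical activities because of arm, shoulder, or hand problems", and 0 means no disability.
- **Eligibility.** Exclusion criteria removes "Patients who indicate to have had impaired wrist function prior to injury". Rheumatoid arthritis, neurological upper-limb disorders and old malunions are given as examples of causes. Further fractures in the injured limb are a separate exclusion. Adults up to 75 are eligible (Inclusion criteria).
- **Timing of the DASH.** Table 1 lists it at 6 weeks and at 3, 6 and 12 months. Data collection and follow up says that baseline characteristics are gathered after randomisation and before treatment, but does not itemise them.
- **Analysis.** Statistical analysis adjusts the one-year DASH for age in an ANCOVA. Randomisation stratifies by three age bands.
- **Reference value.** Sample size states: "The DASH score of an individual without any complaints of the wrist is 0".

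**The concern.** The endpoint is wider than the exclusion. A patient with a long-standing painful shoulder and a sound wrist may enter, and that shoulder adds points to the DASH at one year whichever treatment was given. These points are variation between patients that the treatment cannot affect. A pre-injury score would capture part of it, but none is listed and none is in the model.

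Precision on the primary comparison is at stake, together with the chance that one arm happens to hold more such patients. A later analysis plan cannot repair this, because it cannot adjust for a measure that was never collected, and recall of the pre-injury state fades with time.

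The sentence on the value 0 shows the same mismatch: it treats a whole-limb score as if it were specific to the wrist.

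**Working it through.** **1. The plan's own sample size, and whether the 0 enters it.** The inputs, from Sample size, are:

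- "The mean DASH score after closed reduction and cast treatment after one year of follow up is 19 with a standard deviation (SD) of 18"
- a reduction "by 15 points, from 19 to 4"
- "at α = 0.05% and a power of 90" per cent
- "an estimated lost to follow-up of 10" per cent

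With two-sided 5%: n per arm = (1.960 + 1.282)² × 2 × 18² / 15² = 10.507 × 2.88 = 30.26, so 31. Allowing for 10% loss, 30.26 × 1.1 = 33.3 or 30.26 / 0.9 = 33.6. The stated 33 per arm is reproduced. (The printed 0.05% would need 66 per arm before loss, so 5% was evidently used. That is a separate misprint.) The formula takes the difference of 15 and the SD of 18; the value 0 does not appear in it.

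**2. Precision as planned.** With 45 per arm and 10% loss, about 40 per arm are evaluable (45 × 0.9 = 40.5). The standard error of the difference is 18 × √(2/40) = 4.02 points. Power for 15 points is 0.96.

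**3. Gain from a pre-injury DASH.** Let r be its correlation with the one-year DASH within arm, after age. The documents give no value, so r is assumed. Adjustment multiplies the residual variance by 1 − r², and the equivalent gain in sample size is 1/(1 − r²). Here 18 is taken as the SD before adding the covariate.

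| Assumed r | 1 − r² | Variance removed | Equivalent sample size | SE at 40 per arm | n per arm before loss |
|---|---|---|---|---|---|
| 0 | 1.00 | 0% | 1.00 | 4.02 | 31 |
| 0.3 | 0.91 | 9% | 1.10 | 3.84 | 28 |
| 0.4 | 0.84 | 16% | 1.19 | 3.69 | 26 |
| 0.5 | 0.75 | 25% | 1.33 | 3.49 | 23 |

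The SE column is 4.02 × √(1 − r²). The last column is 30.26 × (1 − r²), rounded up.

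**4. Chance imbalance, by illustration.** Suppose that two of 40 patients in one arm, and none in the other, carry 40 points of prior disability. That arm's mean moves by 2 × 40 / 40 = 2 points, which is 2/15 = 13% of the assumed effect and 2/4.02 = 0.5 of a standard error. Both inputs are assumed.

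**5. The reference value.** Primary outcome makes 0 the absence of disability on a scale that covers arm, shoulder and hand. A person with a healthy wrist and a bad shoulder therefore need not score 0, so the sentence in Sample size does not follow from the protocol's own description.

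**The case against.** The strongest reply is that the trial is valid without this covariate. Prior disability precedes randomisation and is balanced in expectation, so an age-adjusted comparison of one-year scores is unbiased. The SD of 18 comes from real cast-treated patients and may already contain background limb disability; the documents do not say. Power is 0.96 with 40 per arm on the plan's assumptions, so precision is not short. A 2-point imbalance is half a standard error, which is ordinary chance variation already covered by the test. Age stratification and adjustment take out the part of prior disability that goes with age. The wrist-specific PRWE is collected whenever the DASH is, so a DASH difference can be compared with a wrist score. Baseline characteristics are not itemised in this article and Table 1 covers follow-up visits, so a baseline score may be collected without being listed.

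All of this stands, and it limits the point to an improvement in efficiency. It does not remove the point: age is an incomplete proxy for limb disability, and the PRWE does not reduce variance in the primary analysis.

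A reader might infer more than the documents support:

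- *That the sample size rests on a wrong value of 0.* It does not (step 1).
- *That the comparison is biased.* Randomisation rules out systematic bias from this source.
- *That the exclusions deal only with the wrist.* Other fractures of the limb are excluded, and some upper-limb disorders are caught through their effect on the wrist.
- *That background disability puts the assumed plating mean of 4 out of reach and so costs power.* Background points added to both arms leave the difference at 15. Power falls only if the plating mean rises while the cast mean stays at 19, and the documents give no population DASH value to support that.
- *That Benefits and risks contradicts Table 1.* The sentence beginning "Patients will be asked to fill out a DASH form, rate their pain on a Visual Analogue Scale" ends by referring to all visits, but this may attach to the pain-medication estimate alone. The same section places the questionnaires at the Table 1 visits from six weeks on. The wording is ambiguous and the matter clerical.

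**Conclusion.** The point holds as a cheap improvement in precision. It is not an error in any figure the trial relies on. The primary score covers more of the limb than the prior-function exclusion does, and the article neither lists a pre-injury DASH nor adjusts for one. The consequence is residual variance and chance imbalance that could be reduced.

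The size depends on an assumed correlation. At 0.3 to 0.5 the residual variance falls by 9% to 25%, equivalent to 10% to 33% more patients. If most recruits score close to 0 before injury, the correlation and the gain could be smaller. The sentence about 0 is imprecise, but correcting it is editorial.

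**What to change.** 1. At the one-week visit, after consent and before allocation is revealed, have each patient complete the DASH once with reference to the week before injury. List it in Data collection and follow up. The other baseline data are taken after randomisation, so state this item's earlier timing explicitly. If the full protocol already collects such a score, only its timing and item 2 need attention.
2. In Statistical analysis, add pre-injury DASH as a covariate beside age in the primary ANCOVA and in the repeated-measures analysis of DASH trends.
3. In Sample size, say that 0 applies to an individual without upper-limb complaints. No number changes.
4. In Benefits and risks, make clear which item the reference to all visits belongs to.

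The cost is one questionnaire at an existing visit and one model parameter. The article's own estimate is about ten minutes for the DASH, pain scale and medication question together. The downside is recall error, which is independent of arm provided that the form is completed before allocation is known.

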## Background

Fractures of the distal radius account for an estimated 17% of all fractures diagnosed [1,2]. Two-thirds of these fractures are displaced and require reduction [3]. Although extra-articular distal radius fractures are considered to be relatively harmless, inadequate treatment may result in severely impaired function of the wrist [4,5]. The consequences of post-traumatic loss of function are comprehensive, both on individual and societal level, and have long been underestimated [6].

Several treatment modalities to obtain and maintain reduction exist and decision-making is mainly based on fracture type, region and surgeon’s preference [7]. Although good results have been described for both conservative and surgical management, the ideal treatment method remains unknown.

According to current Dutch guidelines, standard treatment for patients with displaced extra-articular distal radius fractures consists of closed reduction and cast immobilisation for four to six weeks [8]. Nevertheless, redisplacement occurs in up to 60% of cases and functional recovery is frequently poor [9-11]. If fracture redisplacement occurs, surgical reduction and fixation is the treatment of choice [8].

A well-established and widely applied surgical approach is open reduction and internal fixation (ORIF). This procedure involves surgical (open) fracture reduction and internal fixation by means of locking plates. Over the past years, the use of volar locking plates has become increasingly popular [12]. This type of osteosynthesis requires a relatively simple volar approach to the wrist, followed by fracture fixation using fixed angle implants [13]. The technique allows more accurate reduction and immediate stable fixation. Subsequent removal of the plate is rarely necessary [7,14]. The fracture stability allows for early mobilisation and may therefore result in an improved recovery of function [7,14]. By 1987 already, Dias et al. concluded that patients who were encouraged to mobilise their injured wrist from the start in a modified cast which only restricted extension, recovered function more quickly than those whose who were immobilised in a conventional plaster cast [10].

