The control group will continue treatment with cast immobilisation according to Dutch guidelines: a circular cast for another four weeks [8]. At one week and three weeks following initial immobilisation, radiographs will be performed in both groups to ensure that loss of reduction has not occurred. Loss of reduction is defined as: >15° dorsal or >20° volar angulation of the distal fracture fragment, >5 mm loss of radial height, or ≤15° radial inclination [8]. If this is the case, operative treatment will be offered. According to Dutch treatment standards, vitamin C 500 milligrams will be prescribed to all patients at initial presentation and for a duration of two months in order to prevent Complex Regional Pain Syndrome [8].

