### Statistical analysis

Patients will be analysed according to the intention-to-treat protocol. General descriptive statistics on patient characteristic at baseline will be performed including factors such as gender and age. The primary outcome, DASH at one year, will be corrected for age and assessed using an analysis of co-variance (ANCOVA). Trends in DASH scores among the different time points will be assessed using a repeated measures ANOVA. The secondary outcomes; PRWE, quality of life (QoL SF-36), pain as indicated on a Visual Analogue Scale (VAS) and Range of Motion (ROM) will be analysed in a similar manner. The radiological outcome, number of conversions and complication rate will be determined using either a Fisher Exact of a Chi square test, depending on the order of magnitude of the results. Subgroup analyses with regard to DASH score will be performed for gender and age for each randomisation stratum.

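### The sample size uses the full 15-point plate-versus-cast difference and makes no allowance for control patients operated on after loss of reduction

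*Protocol article*

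**What the plan says.** All references are to the protocol article.

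- **Sample size, control outcome:** "The mean DASH score after closed reduction and cast treatment after one year of follow up is 19 with a standard deviation (SD) of 18".
- **Sample size, effect:** "We assume that treatment with volar plating will decrease the DASH score which is achieved by conservative cast treatment by 15 points", that is, from 19 to 4. With 90% power and 10% loss to follow-up this gives 33 per arm. The number is then raised to 45 per arm, for safety and natural deaths only.
- **Interventions:** radiographs at one and three weeks check for loss of reduction. "If this is the case, operative treatment will be offered".
- **Background:** "redisplacement occurs in up to 60% of cases", and surgery is named as the treatment of choice when it happens.
- **Secondary outcomes and Statistical analysis:** the rate of cross-overs is an outcome, and the number of conversions is to be tested.
- **Statistical analysis:** "Patients will be analysed according to the intention-to-treat protocol".

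**The concern.** The sample size contrasts patients who were plated with patients who were treated in a cast. The trial compares two policies: plating after randomisation at one week, and cast treatment with surgery offered if reduction is lost. Under intention to treat, a control patient who is operated on counts as a control. If that patient benefits from the operation, the control mean moves towards the plate mean and the expected difference shrinks.

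Conversion is foreseen, yet the printed calculation, which shows its formula, its dropout allowance and the final increase, has no term for it. This is not a detail lost in condensing a longer document.

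Two things are at stake. The stated 90% power may not apply to the comparison the trial will report. And because the stated aim is plating versus closed reduction with plaster, a non-significant result could be read as showing no benefit of plating, when the comparator includes some plating.

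**Working it through.** **Inputs from the document.** Means 19 and 4 (difference 15), SD 18, power 90%, loss 10%, 33 then 45 per arm. Alpha is printed as 0.05%, but only 5% two-sided reproduces the stated number, so 5% is used here. The misprint is a separate matter.

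**Assumptions.** No conversion rate is given, so the share of controls operated on, *c*, runs from 0 to 60%. The top of the range is the Background's ceiling for redisplacement. The age adjustment in the ANCOVA is not modelled, because no correlation with DASH is given.

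**Step 1: reproduce the stated number.** n = (1.96 + 1.282)² × 2 × 18² / 15² = 30.3 per arm. Allowing for 10% loss gives 30.3 × 1.1 = 33.3, or 30.3 / 0.9 = 33.6. The stated 33 is reproduced within rounding, using the full 15 points and no conversion.

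**Step 2: evaluable patients at the planned size.** 45 × 0.9 = 40.5, taken as 40 per arm. The standard error of the difference is 18 × √(2/40) = 4.02.

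**Step 3: dilution.** If converts reach the plate mean, the control mean is 19 − 15c and the intention-to-treat difference is 15 × (1 − c). If they gain half the benefit, it is 15 × (1 − c/2). Power is from the noncentral t distribution with 78 degrees of freedom and noncentrality equal to difference / 4.02.

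| Conversion | Difference, full benefit | Power | Difference, half benefit | Power |
|---|---|---|---|---|
| 0% | 15.0 | 96% | 15.0 | 96% |
| 20% | 12.0 | 84% | 13.5 | 91% |
| 30% | 10.5 | 73% | 12.75 | 88% |
| 40% | 9.0 | 60% | 12.0 | 84% |
| 60% | 6.0 | 31% | 10.5 | 73% |

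**Step 4: how much conversion 90% power tolerates.** With 40 per arm and SD 18, the difference detectable with 90% power is 13.2 points.

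- Full benefit: c = 1 − 13.2/15 = 12%.
- Half benefit: c = 2 × (1 − 13.2/15) = 24%.
- Full benefit, plate-arm SD 8 (an assumption): the standard error is √((18² + 8²)/40) = 3.11, the detectable difference about 10.3 points, and c = 1 − 10.3/15 = 31%. Power is about 97%, 91% and 81% at 20%, 30% and 40% conversion, and just under 50% at 60%.

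**Step 5: a check in the other direction.** A control arm mixing converted and unconverted patients is more variable. With SD 18 within each group, the control variance becomes 18² + c(1 − c) × 15². This lowers power slightly, for example from 84% to 82% at 20% conversion.

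**The case against.** The strongest defence is that the mean of 19 may already be the mean of a cast-first policy. The phrase used for it can describe initial treatment, and the Background gives surgery on redisplacement as the guideline path. If the cited cohort followed that path, 19 already reflects later surgery and little or no further dilution is due. This stands as a possibility. The protocol does not say, and its wording labels the figure as cast treatment.

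Three stronger readings are tempting, and the document does not support them:

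- **A reader might infer that the intention-to-treat difference cannot be 15 points.** That is not shown. It fails if 19 includes later surgery, or if patients operated on after redisplacement do no better than cast patients.
- **A reader might infer that the control arm will be largely plated.** The 60% is an upper bound on redisplacement, not a conversion rate. Surgery is only offered, and with randomisation at one week some redisplacement may come before allocation.
- **A reader might infer that 90% power is lost beyond about 12% conversion.** That holds only with full benefit and SD 18 in both arms. A smaller plate-arm SD is plausible, because an assumed mean of 4 lies close to the DASH floor of 0.

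It can also be said that the protocol states a pragmatic aim, that intention to treat suits it, and that reporting cross-overs would show readers how many controls were operated on. All of that is right, and it limits the risk of misreading. It does not put conversion into the power calculation. The planned 45 per arm does give real reserve (96% without conversion, 84% at 20% with full benefit), but the protocol does not present it as an allowance for conversion.

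A complier-average analysis is not the natural remedy. Surgery on redisplacement is part of the control policy rather than non-compliance. The method would also need converts to have the same outcome with immediate as with later plating, which is doubtful.

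**Conclusion.** The point holds in a limited form. The calculation makes no allowance for conversion, although the protocol foresees it and analyses by intention to treat. A difference below 15 points is therefore likely, subject to the two exceptions concerning the mean of 19 and the benefit in converts.

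How much power is lost cannot be fixed from the document. With full benefit and SD 18, conversion of 20% to 40% raises the type II error from the stated 10% to between 16% and 40%. Under the milder assumptions examined, 90% power survives to about 24% or 31% conversion. The protocol should correct this, but the allocation, the primary analysis and the planned number can stay as they are.

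**What to change.** 1. In Sample size, state the expected share of controls who will be operated on and its basis, and say whether the cited mean of 19 includes patients who had later surgery.
2. Restate power for the intention-to-treat contrast over a range of conversion rates, for example 0 to 60%, giving the assumed benefit in converts and the SD in each arm. Note that 45 per arm (40 analysed) gives 90% power for a difference of about 13 points at SD 18.
3. Word the primary question, and later the conclusion, as immediate plating versus cast treatment with surgery offered on redisplacement.

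This needs no additional patients, no complier-average analysis and no change to clinical management. The cost is a few sentences, one table and a less favourable stated power.

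### The sample size is stated at α = 0.05%, but the 33 patients per arm derived from it fit only a two-sided α of 0.05 (5%), and the article gives no other level

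*Protocol article*

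**What the plan says.** All the relevant statements are in the Sample size section of the protocol article.

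- Level, power and attrition: "Therefore at α = 0.05% and a power of 90%, with an estimated lost to follow-up of 10%, we would require 66 patients". Whether the test is one- or two-sided is not stated.
- Control-arm DASH at one year: the mean "is 19 with a standard deviation (SD) of 18".
- Assumed effect: a reduction "by 15 points, from 19 to 4".
- Result: "66 patients in total and 33 per treatment arm".
- Method: "This figure was calculated using the standard formula for means of superiority trials". The formula printed after this is n = [A + B]² × 2 × SD²/DIFF², with n per arm. Its legend describes A as the significance level and B as the power.
- Enrolment: "For safety measures and to correct for natural deaths, 45 patients in each arm will be included".

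The Statistical analysis section names an age-adjusted ANCOVA for the primary outcome and gives no significance level. No other section gives one either.

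**The concern.** Read literally, 0.05% is 0.0005, one hundredth of the conventional level. A formula that gives about 30 per arm at 5% cannot give nearly the same number at 0.05%. Either the level or the sample size is misprinted, and the stated α, power and sample size cannot all be true.

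This matters because the sample size section holds the only α in the article. A reader who wants to know what the trial was designed to detect, and at what error rate, gets a figure that is wrong by a factor of 100. If the level is corrected only after the results are known, the correction could be taken for a relaxation of the criterion.

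**Working it through.** **Inputs (Sample size section).** SD = 18, DIFF = 15 (19 to 4), power = 90%, loss = 10%, equal arms. Assumptions: the same SD in both arms, and A and B taken as normal quantiles. Sidedness is not stated, so both readings are tried.

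**Constant factor.** 2 × SD²/DIFF² = 2 × 324/225 = 2.88. The quantile for 90% power is 1.282.

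**Step 1: reproduce the stated 33 per arm.** Two-sided α = 0.05, quantile 1.960:

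- n = (1.960 + 1.282)² × 2.88 = 10.507 × 2.88 = 30.26 evaluable per arm.
- With 10% loss: 30.26 × 1.10 = 33.3, or 30.26/0.90 = 33.6.

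This matches 33 per arm and 66 in total, to within rounding.

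**Step 2: the level as printed.** Two-sided α = 0.0005, quantile 3.481:

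- n = (3.481 + 1.282)² × 2.88 = 22.68 × 2.88 = 65.3, so 66 evaluable per arm.
- With 10% loss: 65.32/0.90 = 72.6, so 73 per arm; rounding up first, 66/0.90 = 73.3, so 74. The total is 146 to 148.

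**Step 3: other readings.**

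| Reading (90% power) | Evaluable per arm | With 10% loss (÷ 0.90) |
|---|---|---|
| α = 0.05, two-sided | 30.26 | 33.6 |
| α = 0.05, one-sided | 24.66 | 27.4 |
| α = 0.0005, two-sided | 65.32 | 72.6 |
| α = 0.0005, one-sided | 60.20 | 66.9 |
| α = 0.0005, two-sided, t-based | 68.3 | 75.9 |

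Only two-sided 5% comes near 33. No version at 0.0005 does.

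**Step 4: rounding at 5%.** 33 per arm less 10% leaves 29.7 evaluable, against 30.26 needed. The standard error is 18 × √(2/29.7) = 4.67, and 15/4.67 − 1.96 = 1.25, so power is about 89.5%. Rounding 33.6 up gives 34 per arm (68 in total), and 34 × 0.90 = 30.6 evaluable, which is enough.

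**Step 5: the enrolled sample.** 45 per arm less 10% is 40.5 evaluable. The standard error is 18 × √(2/40.5) = 4.00, and 15/4.00 = 3.75.

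- At two-sided 5%: 3.75 − 1.96 = 1.79, power about 96%.
- At two-sided 0.05%: 3.75 − 3.481 = 0.27, power about 61%.

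**Step 6: the legend.** Putting the level and the power themselves in for A and B gives (0.05 + 0.90)² × 2.88 = 2.6 per arm. The legend therefore cannot be meant literally, and it does not help a reader recover the intended α.

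**The case against.** The strongest reply is that this is a stray percent sign and nothing more. The section's own number shows that the calculation was done at 5%, the conventional level, and the enrolled sample is larger than that calculation requires. Most of this stands. It settles how serious the error is, but it does not make the printed statement right, and nothing else in the article corrects it.

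Three stronger readings are tempting, and the article does not support them.

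- **The trial is badly underpowered.** A reader might infer this from the 61% in Step 5. That figure applies only if the primary test is run at 0.0005, a level which the stated sample size shows was not the one used. At 5% the power is about 96%.
- **A primary result of p = 0.01 would have to be called non-significant.** The 0.05% is a planning input. The Statistical analysis section sets no decision threshold, and the full protocol or analysis plan, not shown here, may give one.
- **A per-arm result of 66 was mislabelled as a total.** The two figures agree by coincidence. The 66 per arm at 0.0005 is before loss, whereas the article's total of 66 already includes 10% loss. Like for like, the comparison is 73 to 74 per arm against 33.

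The loose legend for A and B and the rounding from 33.6 to 33 change no result once 45 per arm are enrolled. They are worth correcting only because the same sentences are being edited.

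**Conclusion.** The point holds as a misprinted design parameter. At the printed α of 0.05%, the section's formula needs about 66 evaluable patients per arm, or 73 to 74 with loss, which is more than twice the stated 33. At a two-sided α of 0.05 it reproduces 33 to within rounding, so the level is almost certainly what is wrong and the sample size is not.

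This rests on the stated SD, difference, power and loss, on normal quantiles, and on a two-sided test. The last is inferred: at 5%, only the two-sided version gives 33. The error calls for a correction of wording. It is not evidence of an inadequate design, since the planned enrolment gives about 96% power for 15 points at 5% under the article's own assumptions.

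**What to change.** In the Sample size section:

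1. Replace the printed level with a two-sided α of 0.05 (5%), after confirming against the original calculation that this was the level used.
2. Define A and B as the standard normal quantiles for the significance level and the power, 1.96 and 1.28.
3. Give the requirement as 30.26 evaluable per arm, rounded up to 34 per arm (68 in total) after 10% loss.

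The cost is a sentence or two of text. The planned 45 per arm stays as it is. The correction is best made and dated before the one-year data are analysed.
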